## Abstract

**Background:**

There is ongoing debate regarding the treatment of severe and multiple traumatized children and adolescents with post-traumatic stress disorder (PTSD). Many clinicians favor a phase-based treatment approach (i.e., a stabilization phase prior to trauma-focused therapy) over immediate trauma-focused psychological treatment, despite the lack of scientific evidence. Research on the effects of different treatment approaches is needed for children and adolescents with (symptoms of complex) PTSD resulting from repeated sexual and/or physical abuse during childhood.

**Objective:**

This paper describes the rationale, study design, and methods of the MARS-study, a two-arm randomized controlled trial (RCT) that aims to compare the results of phase-based treatment with those of immediate trauma-focused treatment and determine whether immediate trauma-focused treatment is not worse than phase-based treatment in reducing PTSD symptoms.

**Methods:**

Participants are individuals between 12 and 18 years who meet the diagnostic criteria for PTSD due to repeated sexual abuse, physical abuse, or domestic violence during childhood. Participants will be blindly allocated to either the phase-based or immediate trauma-focused treatment condition. In the phase-based treatment condition, participants receive 12 sessions of the Dutch version of Skill Training in Affective and Interpersonal Regulation (STAIR-A), followed by 12 sessions of EMDR therapy. In the immediate trauma-focused condition, the participants receive 12 sessions of EMDR therapy. The two groups are compared for several outcome variables before treatment, mid-treatment (only in the phase-based treatment condition), after 12 trauma-focused treatment sessions (post-treatment), and six months post-treatment (follow-up). The main parameter is the presence and severity of PTSD symptoms (Clinician-Administered PTSD Scale for Children and Adolescents, CAPS-CA). The secondary outcome variables are the severity of complex PTSD symptoms (Interpersonal Problems as measured by the Experiences in Close Relationship-Revised, ECR-RC; Emotion Regulation as measured by the Difficulties in Emotion Regulation Scale, DERS; Self Esteem as measured by the Rosenberg Self Esteem Scale, RSES), changes in anxiety and mood symptoms (Revised Anxiety and Depression Scale; RCADS), changes in posttraumatic cognitions (Child Posttraumatic Cognitions Inventory, CPTCI), changes in general psychopathology symptoms (Child Behavior Checklist, CBCL), and Quality of Life (Youth Outcome Questionnaire, Y-OQ-30). Furthermore, parental stress (Opvoedingsvragenlijst, OBVL) and patient-therapist relationship (Feedback Informed Treatment, FIT) will be measured, whereas PTSD symptoms will be monitored in each session during both treatment conditions (Children’s Revised Impact of Event Scale, CRIES-13).

**Discussion:**

Treating (symptoms of complex) PTSD in children and adolescents with a history of repeated sexual and/or physical abuse during childhood is of great importance. However, there is a lack of consensus among trauma experts regarding the optimal treatment approach. The results of the current study may have important implications for selecting effective treatment options for clinicians working with children and adolescents who experience the effects of exposure to multiple interpersonal traumatic events during childhood.

**Trial registrations:**

The study was registered on the “National Trial Register (NTR)” with the number NTR7024. This registry was obtained from the International Clinical Trial Registry Platform (ICTRP) and can be accessed through the ICTRP Search Portal (https://trialsearch.who.int/).

## Background

A meta-analysis of children and adolescents exposed to traumatic events indicated that 16% developed post-traumatic stress disorder (PTSD) [1]. Adolescents with PTSD re-experience traumatic events, avoid memories of the trauma, develop negative thoughts and moods, and are hypervigilant about potential threats [2]. Adolescents who have been exposed to (repeated) sexual abuse, maltreatment, and/or domestic violence are at an even higher risk of developing PTSD symptoms [1]. Beyond the core symptoms of PTSD, adolescents are prone to developing a range of additional challenges, including poor self-esteem, difficulties in interpersonal relationships, and struggles with emotion regulation. Collectively, these symptoms are commonly referred to as characteristics of the ICD-11 classification Complex PTSD [3, 4].

Although unprocessed trauma can significantly impact a child's development, several studies have demonstrated the effectiveness of trauma-focused treatments, such as eye movement desensitization and reprocessing (EMDR) therapy, trauma-focused cognitive behavioral therapy (TF-CBT), and Prolonged Exposure [5, 6], in treating childhood PTSD. As a result, trauma-focused treatments are generally recommended in national guidelines for children and adolescents [7] and international guidelines from reputable organizations, such as the International Society for Traumatic Stress Studies [8] and the National Institute for Health and Clinical Excellence [9]. However, it is worth noting that most studies underlying these guidelines have primarily focused on children and adolescents who developed PTSD due to a single traumatic event, leaving a knowledge gap regarding the efficacy of trauma-focused therapies for children and adolescents with Complex PTSD and a lack of consensus on the preferred treatment approaches for this population.

A position paper by the International Society of Traumatic Stress Studies [10] highlighted the insufficient evidence available to support a specific treatment for Complex PTSD in children and adolescents. This dearth of evidence has sparked long-standing debate among clinicians and researchers regarding the optimal approach for treating Complex PTSD. Recognizing the potential limitations of existing evidence-based treatments for children and adolescents with Complex PTSD and severe clinical presentations, the ISTSS argues that modifications to trauma-focused treatments may be necessary to address the symptoms of Complex PTSD effectively [10]. Consequently, various phase-based treatment models have been developed for children and adolescents with Complex PTSD [11, 12]. These models generally prioritize the enhancement of emotional and interpersonal regulation skills as well as strengthening self-esteem before embarking on trauma-focused treatment. However, it is important to note that a comprehensive body of compelling evidence supporting the efficacy of phase-based models for the treatment of Complex PTSD is lacking [13]. Critics of phase-based models state that research on adults with Complex PTSD has shown that the incorporation of regulation skills training prior to trauma-focused therapy unnecessarily prolongs therapy [14–16]. In addition, studies using trauma-focused treatment in adolescents have demonstrated promising results in the treatment of PTSD and Complex PTSD with a history of (repeated) sexual abuse and maltreatment [17–20], albeit with inconsistent findings and variations in the adaptation of treatment models.

Hence, the limited number of studies investigating the effectiveness of treatments for young individuals with Complex PTSD underscores the need for further research [10]. In their position paper published in 2019, the ISTSS deemed treatment recommendations premature because of current knowledge gaps. This indicates a pressing requirement for research exploring the effects of trauma-focused treatment on adolescents with (symptoms of complex) PTSD resulting from (repeated) sexual abuse, maltreatment, and/or domestic violence. To address this research gap, the present study describes an RCT aimed at investigating the differences in treatment effects between two treatment approaches (i.e., phase-based versus immediate trauma-focused) in adolescents with (symptoms of complex) PTSD resulting from a history of repeated sexual and/or physical abuse during childhood.

The primary objective of this study is to compare the results of phase-based treatment with those of immediate trauma-focused (i.e., eye movement desensitization and reprocessing; EMDR) therapy using a two-arm randomized controlled trial design. The first aim is to determine whether immediate trauma-focused treatment is not worse than phase-based treatment in reducing PTSD symptoms. If trauma-focused treatment is found to be equally effective when applied, it could lead to significant reductions in treatment duration. Second, we aim to investigate whether the phase-based therapy approach yields superior outcomes compared to the direct trauma-focused condition in terms of Complex PTSD symptoms, including emotion regulation, interpersonal problems, and self-esteem. Additionally, we will examine comorbid symptoms and dropout rates as secondary outcome measures. The third objective of the current study is to identify potential moderators and predictors of dropout or treatment responses/non-responses under both treatment conditions. We hypothesize that the presence of affect dysregulation and interpersonal problems at the beginning of therapy will be associated with poorer outcomes in the direct trauma-focused condition. Finally, we will examine the relationship between the reduction of posttraumatic stress symptoms in adolescents and a decrease in self-reported parental/caretaker stress. This objective addresses the clinical assumption that managing parental stress should be prioritized before initiating PTSD treatment in adolescents.

## Method

### Study design

This study entails a single-blind, randomized controlled trial with two arms: a phase-based treatment condition (TRAP followed by EMDR) and a trauma-focused treatment condition (EMDR only). In the TRAP-EMDR condition, participants receive 12 sessions of skills training (TRAP; the Dutch adolescents version of the STAIRS protocol), followed by 12 sessions of EMDR therapy. In the other condition, the participants receive 12 EMDR sessions. The two groups will be compared for several outcome variables before treatment, immediately after 12 sessions (post-treatment), and six months post-treatment (follow-up) (see Fig. 1). This study will be coordinated by the Karakter Academic Center for Child and Adolescent Psychiatry in the Netherlands. The study started in 2018, paused for seven months in 2020 due to COVID-19, and continued in September 2020. This study is ongoing and is expected to be completed by 2024.

**Fig. 1 Fig1:**
[figure not shown]
Flowchart of the MARS-study

### Participants

Participants are individuals between 12 and 18 years of age, meeting the criteria for PTSD (according to the Diagnostic and Statistical Manual of Mental Disorders, fifth edition), and victims of repeated sexual and/or physical abuse and/or domestic violence in childhood. Participants are recruited from different departments of Karakter, a large mental health organization for children and adolescents in the Netherlands. This applies the following inclusion criteria: (1) meeting the criteria for PTSD, assessed with the Clinical-Administered PTSD Scale for Children and Adolescents (CAPS-CA); (2) reporting a history of (repeated) physical and/or sexual abuse and/or domestic violence by a caretaker, family member, or person in authority; (3) the availability of a non-offending adult caregiver for the treatment, as the presence of a caregiver is part of the treatment design; (4) motivation and ability of the participant and the caregiver to attend weekly treatment sessions; (5) safe living circumstances to minimize the risk of retraumatization during the study; and (6) participants and caregivers have sufficient command of the Dutch language to participate in the treatment.

Exclusion criteria are (1) acute suicidal behavior or suicidal ideations requiring immediate hospitalization; (2) severe head trauma indicated by a score < 9 on the Glasgow Coma Scale as known from the participant’s medical history, to avoid brain dysfunction or retrograde amnesia of the traumatic event due to head injury; (3) concurrent psychotherapy during the study; (4) current severe mental disorder in the participant’s main caregiver (as evaluated by the responsible clinician), such as psychosis, severe episode of depression, or severe substance abuse, to assure the ability of the caregiver to participate in the treatment; (5) a sibling of the participant already participating in the study (to avoid the transference of treatment effects if siblings are randomized in different conditions); and (6) intellectual disabilities (IQ < 70).

### Randomization

Once the informed consent form is signed and the baseline questionnaires (T0 and T1) are completed, the randomization procedure begins. Participants are randomly assigned to either a control or an experimental group with a 1:1 allocation according to a computer-generated randomization schedule stratified by sex (male or female) and psychiatric diagnoses and using permuted blocks of random sizes. The block sizes will not be disclosed to ensure concealment. Participants will be randomized using randomization.com, an online randomization tool. Allocation concealment will be ensured because the person who performs randomization has no other role in the study. This person will prepare the randomization lists and seal the envelopes. The randomization code will not be released until the participant is recruited into the trial, which occurs after all baseline measurements have been completed.

To ensure allocation concealment, the steps involved in randomization, outcome measurements, and treatment are separated. Participants who meet the inclusion criteria and provide consent for participation will be randomized. Research assistants responsible for recruitment and outcome measurement will request randomization.

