### Sample size and power

This study implemented a non-inferiority trial. A non-inferiority trial is a type of clinical research study that aims to demonstrate that a (new) treatment is not worse than an existing treatment by a prespecified margin. Because the non-inferiority margin for CAPS-CA-5 scores had not yet been determined at the start of this study, we used the article published by Sloan et al. [44] to estimate the non-inferiority margin. The primary outcome was the total score on the Clinician-Administrated PTSD Scale for DSM-5 (CAPS-5). Non-inferiority was defined as a score of 10 points. However, the results showed that during follow-up, a non-inferiority margin of five points would have been sufficient to yield the same conclusion. Therefore, based on the article by Sloan et al. [44] and clinical reasoning, the largest clinically acceptable effect to declare non-inferiority is a change in the CAPS-CA-5 score of five points (d). Based on the study by Sloan and colleagues, the true mean difference (μ_B_-μ_A_) between the treatments is -1.82 (after 12 weeks). In a non-published pilot study of 17 adolescents, we calculated a mean total score on the CAPS-CA-5 of 38.2 with a standard deviation of 10.4 (σ). An equal number of participants will be included in both arms of the trial (r = 1).

For the estimation of the sample size (for 80 percent power and type 1 error of 2,5 percent) the following formula is used [45].$${n}_{A}=\frac{7.85{\sigma }^{2}\left(r+1\right)}{{\left(\left({\mu }_{B}-{\mu }_{A}\right)-d\right)}^{2}r}$$

According to this formula, 36,5 participants per arm are required. As in the previous sample size calculation, we used the baseline variables as covariates. Based on Borm et al. [46, 47] we estimate that the design factor will be equal to 0.75, because we assume a correlation of 0.5 between the two measurements. Hence, we would need 36.5*0.75 = 27.4 participants per group. To compensate for an unknown clustering effect and unknown psychometric properties, and given the need to compensate for an expected dropout rate, we plan to include 40% more participants (76 participants in total), so that 38 participants will be recruited per arm.

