### Statistical analysis

Data will be analyzed using SPSS V.29.0 for Windows (SPSS Incorporated). Pretreatment group differences with respect to age, sex, ethnicity, and type of traumatic event will be assessed using independent-sample t-tests for continuous data and χ^2^ tests for categorical data. Before testing, we will check all the data according to the appropriate assumptions.

To answer the primary question, a repeated-measures ANCOVA will be conducted. Baseline scores will be included as covariates, time as a categorical variable, and treatment condition as a fixed effect. The intercept will be treated as a random effect. We will examine the residuals to assess the model assumptions and goodness-of-fit. *P-values* will be reported to four decimal places, with *P-values* less than 0.001 reported as *p* < 0.001. For all tests, we will use 2-sided *P-values* with alpha =  < 0.05 level of significance. As this is a non-inferiority trial, both intention-to-treat and per-protocol analyses will be performed.

To evaluate the secondary outcomes, a repeated-measures ANCOVA will be conducted for the total score on the ECR-RC, DERS, RSES, RCADS, CPTCI, CBCL, OBVL, and Y-OQ-30. Baseline scores will be included as covariates, time as a categorical variable, and treatment condition as a fixed effect. The intercept will be treated as a random effect. We examine the residual to assess the model assumptions and goodness-of-fit. Delta-scores for pre- to post-treatment (T1 and T3) will be calculated, and an independent sample t-test will be used to compare the TRAP + EMDR and EMDR-only conditions. For the calculation of effect sizes (Cohen’s *d*) for within-group effects, we will divide the difference in means between pre- and post-treatment by the standard deviation of the difference in means. *P-values* will be reported to four decimal places, with *P-values* less than 0.001 reported as p < 0.001. For all tests, we will use 2-sided *P-values* with alpha =  < 0.05 level of significance.

To determine PTSD symptom changes on the CRIES-13, we will analyze the data for all time points in a linear mixed model. Time, treatment condition, the interaction term time × treatment condition, and sex will be entered as fixed factors, and age as a covariate in the model. The impact of missing data on outcome measurements will be evaluated using different methods, such as Last Observation Carry Forward (LOCF) and Multiple Imputation (MI).

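### Allocation is stratified by sex and psychiatric diagnoses, but the primary and secondary models contain neither factor and the CRIES-13 model omits diagnosis

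*Protocol article*

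**What the plan says.** **Allocation.** In the protocol article, Randomization, participants are assigned 1:1 from a "computer-generated randomization schedule stratified by sex (male or female) and psychiatric diagnoses", "using permuted blocks of random sizes". The number of diagnosis levels is not given.

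**Primary and secondary models.** Under Statistical analysis, the CAPS-CA model is specified term by term: "Baseline scores will be included as covariates, time as a categorical variable, and treatment condition as a fixed effect". A further sentence adds: "The intercept will be treated as a random effect". The same terms are repeated for the secondary outcomes. Neither list contains sex or diagnosis.

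**CRIES-13 model.** This mixed model has time, condition and their interaction, "and sex will be entered as fixed factors, and age as a covariate in the model". Diagnosis is absent here too.

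**Available data.** Under Demographics, sex and the child's diagnoses are both among the variables to be collected.

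**Clustering.** Under Sample size and power, the 40% inflation is justified by three things together: "To compensate for an unknown clustering effect and unknown psychometric properties, and given the need to compensate for an expected dropout rate". The unit of clustering is not named.

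**The concern.** Stratified blocks make the arms alike on sex and diagnosis, which lowers the true sampling variance of the treatment difference if those factors predict CAPS-CA. A model without the factors cannot see this. It leaves the between-strata variation in the residual and reports a standard error suited to unstratified allocation. The confidence interval compared with the five-point margin is then wider than the design warrants.

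The article states its model terms explicitly, so this is a mismatch between stated design and stated analysis rather than a detail passed over in a condensed text. The CRIES-13 model shows that covariates were considered, since sex appears there and not in the primary model. At stake is efficiency: a trial of 76 participants could miss non-inferiority because the analysis gives away precision that the randomization bought.

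**Working it through.** **1. The plan's own figures** (all inputs from Sample size and power: SD 10.4, true difference −1.82, margin 5, r = 1, power 80%, one-sided error 2.5%, design factor 0.75)

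- n per arm = 7.85 × 10.4² × 2 / (−1.82 − 5)² = 36.5, as stated.
- 36.5 × 0.75 = 27.4, as stated.
- 27.4 × 1.40 = 38.4, stated as 38 per arm and 76 in total.

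The sample size reproduces and is not in dispute.

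**2. Set-up for the omitted strata**

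- Residual SD after baseline adjustment: 10.4 × √0.75 = 9.007.
- Distance from the assumed truth to the margin: 5 + 1.82 = 6.82.
- R² is the share of the residual variance, with the baseline score already in the model, that the strata explain. The documents give no value. I assume 10%, with a range of 5% to 15%.
- Strata are taken as balanced between arms, and the normal approximation is used.

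With 27.4 per arm:

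- SE reported by the unadjusted model: SE_rep = 9.007 × √(2/27.4) = 2.433.
- True SE under stratified allocation, which the adjusted model also reports: SE_true = SE_rep × √(1 − R²). At R² = 10% this is 2.308.

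**3. Formulas**

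- True one-sided error, unadjusted: 1 − Φ(1.96 / √(1 − R²)).
- Power, unadjusted: Φ((6.82 − 1.96 × SE_rep) / SE_true).
- Power, adjusted: Φ(6.82 / SE_true − 1.96).

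At R² = 10%:

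- Error: 1 − Φ(1.96 / 0.9487) = 1.9%.
- Unadjusted power: Φ((6.82 − 4.769) / 2.308) = Φ(0.888) = 81.3%.
- Adjusted power: Φ(2.954 − 1.96) = Φ(0.994) = 84.0%.

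**4. Results at 27.4 per arm**

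| R² (assumed) | True one-sided error, unadjusted | Power, unadjusted | Power, adjusted | Gain (points) |
|---|---|---|---|---|
| 0% | 2.5% | 80.0% | 80.0% | 0 |
| 5% | 2.2% | 80.6% | 82.0% | 1.4 |
| 10% | 1.9% | 81.3% | 84.0% | 2.7 |
| 15% | 1.7% | 82.0% | 86.0% | 4.0 |

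The interval from the adjusted model is narrower by 1 − √(1 − R²): 2.5%, 5.1% and 7.8% at the three non-zero values.

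**5. If all 38 per arm are analysed**

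SE_rep = 9.007 × √(2/38) = 2.066. At R² = 10%, power is 92.1% unadjusted and 93.6% adjusted, a gain of about 1.4 points. The benefit shrinks as the number analysed rises.

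**The case against.** **The effect is small and in the safe direction.** This stands. Omitting the factors lowers the one-sided error and does not bias the estimate. A reader might infer that the mismatch threatens the validity of a non-inferiority claim, but it does not: a claim made from the unadjusted model would have been tested more strictly than planned.

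**The gain is easily overstated.** This also stands. It is tempting to set 84.0% against the planned 80% and call the loss four points at R² = 10%. Stratified allocation lowers the true variance of the unadjusted estimate as well, so the right comparison is with 81.3%.

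**The prognostic strength is assumed.** The documents offer nothing on how much sex or diagnosis adds once baseline CAPS-CA is in the model. At R² = 0 nothing is gained.

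**A diagnosis term has a cost.** With 76 participants and an unstated number of levels, some cells may be sparse. The normal approximation ignores the degrees of freedom used. This calls for a collapsing rule, not for leaving the factor out.

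**Clustering.** The plan enlarges the sample "To compensate for an unknown clustering effect and unknown psychometric properties", yet no therapist or department term appears in the models. A reader might infer that ignored therapist clustering raises the risk of a false non-inferiority claim. The documents do not support that. They name no cluster unit and give no number of providers, cluster size or intraclass correlation. They do not say that providers work in one arm only. Both arms deliver EMDR, so shared providers are plausible, and ignoring them would then tend to be conservative. No error rate can be attached to this.

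**Conclusion.** The point holds as a modest loss of efficiency. The randomization uses two stratification factors that the primary and secondary models omit, and the CRIES-13 model takes up only one of them. If the strata explain 5% to 15% of the residual variance, the unadjusted test runs at a true one-sided error of 2.2% to 1.7% and gives up 1.4 to 4.0 points of power at 27.4 per arm, and less if more participants are analysed. These sizes rest on the assumed R², on strata balanced between arms and on a normal approximation. The mismatch itself rests only on the text. It is worth correcting because the correction is cheap. It does not call the sample size or the validity of the trial into question, and the documents give no basis for a conclusion about clustering.

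**What to change.** - Add sex and the diagnosis stratum, coded as used at randomization, as fixed effects to the CAPS-CA model and to every secondary-outcome model.
- Add the diagnosis stratum to the CRIES-13 model.
- State the diagnosis levels and pre-specify, before unblinded data are seen, a rule for collapsing sparse ones.
- Optionally, if the treatment provider is recorded, add a provider random intercept as a sensitivity analysis. The article does not list provider among its study variables, so this would need confirming first.

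The main change is to the analysis wording. Sex and diagnoses are already to be collected, and the strata as used should be recoverable from the randomization lists. The statistical cost is a few degrees of freedom. Design, sample size and conduct are unaffected.
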